### Exclusion criteria

Patients will be excluded if they have: a) a score between 25–32 points on the NIHSS [34] and grade/degree 5, according to the Rankin scale [41]; b) cognitive deficits (a score below 24 points on the Mini Mental State Examination) [42]; c) an inability to actively carry out wrist flexing/bending, that is, metacarpophalangeal and interphalangeal active extension of 10° to 20° wrist extension.

In addition, exclusion criteria relating to contraindications of neurostimulation will be applied, following the safety guidelines [9, 13]: a) use of psychoactive drugs, as stated in the recommendations; b) patients with implanted metallic or electronic devices; c) cardiac pacemaker; d) seizures; e) acute eczema under the electrodes, the presence of tumors, epilepsy or substance abuse; f) pregnancy (this condition was specifically enlisted as a contraindication in this study as a precaution, as there are no data on maternal and fetal effects of tDCS on pregnant women who have suffered a stroke).

### Recruitment

A sample of volunteer participants will be recruited from hospitals and rehabilitation clinics, linked to the local public health system, as well as by study information provided on websites, newspapers, and radio. There will also be referred local support groups, outpatient, and community programs aimed at stroke treatment.

In addition, health professionals from the referred locations where this study will be performed (hospitals and rehabilitation clinics) will disseminate the research among their patients who have suffered stroke. After prior written consent, patients interested in participating will have their records analyzed and will be contacted for inclusion in the study, according to the eligibility criteria. Thus, medical records will only be accessed with prior consent, avoiding possible bias and disregard for privacy legislation, as pointed out by Kho et al. [43].

### Ethics, study registration, and participant consent

The study is being conducted in accordance with the principles of the Helsinki Declaration [44] and the guidelines of Good Clinical Practice (GCP) of the International Conference on Harmonization of Technical Requirements for Registration of Pharmaceuticals for Human Use (ICH) [45]. The study was approved by the local Ethics Committee of the University of Paraíba (number 30163714.0.0000.5188; João Pessoa, Brazil), and is registered in the ClinicalTrials.gov database (NCT02156635). We followed the SPIRIT (Standard Protocol Items: Recommendations for Interventional Trials) guidelines for writing clinical trial protocols [46].

All participating patients will give written informed consent. During the consent, the researcher clarifies the objectives and the procedures to be used in research, with details of the methods to be used, the risks and benefits, and stating the possibility of inclusion in a control or experimental group. The consent also provides a full guarantee of freedom for the participant to refuse to participate or withdraw their consent at any stage of the research, without any penalty, and shall maintain the confidentiality and privacy of the participants during all phases of the research. All participants will receive a copy of the consent form approved by the responsible Ethics Committee. To guarantee that all details of the study process were understood, the researcher has formulated open questions to ask participants on the content of the consent, and only those who answer correctly and sign the document may enter the study.

The study results will be presented at conferences and published in international peer-reviewed journals regardless of the direction and magnitude of the effect.

### Outcomes

For analysis of the primary endpoint, the Barthel index (BI) was chosen because it is commonly used in studies related to post-stroke rehabilitation, adequately reflecting clinical practice [47–49]. This instrument is designed to assess the patient’s level of independence to perform ten basic life activities: eating, bathing, personal care, ability to dress themselves, motility, urinary regularity, bathroom use, chair-bed transfer and vice versa, mobility, and climbing stairs [50]. The literature on the minimal clinically important difference detected by the BI shows that a change of 2 points is meaningful and beyond measurement error. This calculation refers to a modified BI with scores of 0–20 points [51]. Since the changes in the values of the scores do not affect other properties of the scale, it is considered equivalent to the original version, with scores of 0–100 points [52]. Thus, taking the original scale used in this study as a reference, clinical improvement will be considered as a final score higher than 10 points (T2) according to the BI, compared to baseline (T0) before the therapeutic protocol [30].

The BI has been reported with excellent levels of reliability, validity, and adequate responsiveness to change in several countries [52, 53]. In a study of 121 patients at four post-stroke period points (14, 30, 90, and 180 days), the inter-rater reliability using a weighted kappa varied from 0.53 (adequate) to 0.94 (excellent). The inter-rater reliability for the total score, calculated using the intraclass correlation, was 0.94 (excellent). The internal consistency, calculated using Cronbach’s alpha, was excellent, varying between 0.89–0.92 [54]. The construct validity was also confirmed by Wilkinson et al. [55], with rank correlation coefficients of the BI with the SF-36 (Medical Outcomes Study 36-item Short-Form Health Survey) subscales being found in patients with their first-ever stroke varying from r = 0.22 (Role Emotional subscale) to 0.81 (Physical Functioning Profile subscale).

Secondary outcome measures include the Modified Ashworth Scale, the 30-item Motor Activity Log, the Biodex Balance electronic platform, the Postural Assessment Scale for Stroke, the Falls Efficacy Scale, the Medical Research Council scale, the Short Physical Performance Battery, the Wolf Motor Function Test, and the SF-36.

The Modified Ashworth Scale, used in semiotic clinics for spasticity evaluation, evaluates the tone in grades of 0-4 points, and is widely used in clinical practice with adequate test-retest and inter-rater reliability [56–58].

The 30-item Motor Activity Log measures the spontaneous use of the affected limb. Each item asks about the frequency and quality of movement in daily activities of the paretic upper limb. Scores on this measure have adequate reliability and validity in individuals with stroke [59, 60].

The Biodex Balance electronic platform measures the static and dynamic balance through different levels of stability, such as anteroposterior and mediolateral. This instrument is used in several studies involving tDCS applied to stroke [61, 62].

The Postural Assessment Scale for Stroke (PASS) for postural control [63] contains 12 items with progressive levels of difficulty, involving three fundamental postures (lying, sitting, and standing).

The Falls Efficacy Scale measures the fear of falling in 16 ADLs. The total score can vary from 16 (no concern) to 64 (extreme concern) [64, 65].

The force scale from the Medical Research Council (MRC) consists of manual muscle testing, varying from 0 (no movement is observed) to 5 (normal force against the total resistance), with a maximum score of 60 points [66].

The Short Physical Performance Battery (SPPB) consists of three tests that evaluate the static standing balance, gait speed in normal step, and, indirectly, the muscle strength of the lower limbs. Each domain varies from 0 to 4 points, and the maximum total score indicates better physical performance [67, 68]. Gait velocity is a relevant indicator of function and prognosis after stroke [69], meaning that the SPPB is an important tool for assessment of lower extremity motor recovery [70–72].

The Wolf Motor Function Test (WMFT) assesses the speed of task execution through time, the quality of movement, and the strength of grip and shoulder flexion in specific tasks. The WMFT tasks should be filmed with a camera placed at standard position and distance, and the score of the tasks are given from video analyzes [73, 74].

The SF-36, a multidimensional questionnaire to analyze the state of health, consists of 36 items encompassing 8 components, with a final score of 0 (worst state) to 100 (best state) [75].

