## Methods

### Overview

This is a placebo-controlled, double-blind, randomized clinical trial (Fig. 1), in which 40 patients are divided into two groups of 20 participants each. In Fig. 1, the CONSORT (Consolidated Standards of Reporting Trial) flowchart [32] shows the number and distribution of participants: Group A1 - participants in post-stroke subacute stage that receive active tDCS combined with CIMT; Group A2 - participants in the post-stroke subacute stage who receive a placebo stimulation associated with CIMT. Patients will undergo three assessments: baseline (T0), week 2 (T1), and week 4 (T2). Neuropsychological tests will be performed at T0 and T2. Adverse events will be measured in each session, where the researcher responsible for administering the neurostimulation will question the patient on whether they experience any uncomfortable or painful sensation, and if this is related to the tDCS, following the procedure of Brunoni et al. [33]. At the end of the study, participants who received tDCS and showed clinical improvement will be invited to receive bimonthly stimulation for 12 months as part of a longitudinal study of tDCS for stroke. Those who received the tDCS placebo and did not respond will be invited to receive daily sessions with an active current for 10 days. Finally, those who had a response to the placebo will be referred for other physical therapy treatment.

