Regarding safety, deleterious adverse and cognitive effects will be recorded/computed in terms of the proportion in each group, in each time period (T0, T1, and T2), and will be analyzed by the Fisher exact test.

Bias-generating will be tested. The statistical model used for blinding effectiveness was based on the study of Brunoni et al. [97]. The chi-square test or Fisher’s exact test will be used to assess if tDCS blinding guessing was beyond chance for patients, external judges, and trialists. Paired *t*-tests will be used to compare the rate of their guessing according to the Likert scale. Logistic regressions exploring the factors associated with “correct blinding guessing” (that is, participants who correctly guessed their allocation group) will be performed. The factors will be clinical response, high guessing confidence (scores 4 or 5 on the Likert scale), and adverse effects.

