### Sample size

The sample size was estimated based on previous studies using matched groups of non-invasive stimulation with rehabilitation [98, 99]. The power calculations to determine the number of participants in each group were determined in relation to the expected change in BI because it is commonly used in tDCS studies of patients after stroke [30, 31].

According to Khedr et al. [30], the mean expected improvement is about 10 points, with a standard deviation (SD) equivalent to 7 points. Thus, a calculation considering 90 % power suggests that it would take at least 12 patients in each group to detect the difference found corresponding to the effect of active or placebo tDCS.

Considering the possibility of sample loss during the study (withdrawal, inability to continue the treatment, mortality), 20 patients will be included per group, totaling 40 participants (SPSS Ver.20.0; SPSS Inc., Chicago, IL, USA). The analysis will be performed at a 0.05 significance level.

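### The Barthel improvement rule is worded as more than 10 points, although the meaningful change it is derived from converts to exactly 10

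*Protocol article*

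**What the plan says.** The Outcomes section builds the rule in three steps. It first reports from the literature that "a change of 2 points is meaningful and beyond measurement error". It then names the scale: "This calculation refers to a modified BI with scores of 0–20 points". Finally it carries the value to the scale used in this trial, on the ground that "it is considered equivalent to the original version, with scores of 0–100 points". From this it concludes that "clinical improvement will be considered as a final score higher than 10 points (T2) according to the BI, compared to baseline (T0"). An earlier tDCS trial is also cited at that point.

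The label appears to be used in two places:

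- **Data analyses**, in the logistic regression of correct allocation guesses: "The factors will be clinical response, high guessing confidence", with adverse effects as the remaining factor.
- **Overview**, for the offers after the trial: "participants who received tDCS and showed clinical improvement will be invited to receive bimonthly stimulation for 12 months". The offers to placebo participants also depend on whether they responded.

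The primary analysis compares mean change in total BI score, with baseline as covariate. The Sample size section rests on a change in BI: "the mean expected improvement is about 10 points, with a standard deviation (SD) equivalent to 7 points". Neither uses the improvement cut-off.

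**The concern.** The premise says that a change equal to the converted value is already meaningful. The conclusion, read literally, asks for more than that value. The article presents the rule as following from the conversion and gives no reason for a stricter cut-off.

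A strict inequality matters little on a fine scale. On a coarse one it can move the effective threshold by a whole scoring step, and several participants may sit on the boundary. Two analysts could then classify the same patient differently. In a trial of 40, a few such patients can alter the response factor in the blinding regression. Settling the boundary after unblinding would look data-driven.

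**Working it through.** **Inputs.** Meaningful change 2 points on 0–20; trial scale 0–100, treated as equivalent (Outcomes). Improvement about 10, SD 7, 90% power, 12 per group, significance level 0.05 (Sample size; two-sided is my assumption). The scoring step of the 0–100 BI is not given, so two cases are shown.

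**Step 1: the plan's threshold.** Scale factor = 100/20 = 5, and 2 × 5 = 10. The value 10 reproduces. The conversion supports a change of 10 or more; it does not produce a change above 10.

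**Step 2: smallest change that satisfies the literal rule.**

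- If the 0–20 version is scored in whole points, the 5:1 equivalence gives 5-point steps. The next value above 10 is 15, and 15/5 = 3 points on the 0–20 scale.
- On a 1-point grid, the next value above 10 is 11.

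**Step 3: what the figure of 10 stands for in the sample size.** The normal approximation gives n = 2 × (1.960 + 1.282)² × 7²/10² = 10.3, so 11 per group. The two-sample t-test gives 11.35, so 12 per group. The stated 12 reproduces when 10 is the difference between arms. The mean change within an arm is therefore not fixed by the article, and a range is needed.

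**Step 4: share of patients at exactly 10.** Assume a normal change with mean m and SD 7, rounded to the grid.

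- 5-point grid: P(exactly 10) = Φ((12.5 − m)/7) − Φ((7.5 − m)/7)
- 1-point grid: P(exactly 10) = Φ((10.5 − m)/7) − Φ((9.5 − m)/7)

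For m = 10 these are 0.640 − 0.360 = 0.279 and 0.528 − 0.472 = 0.057.

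| Assumed mean change | 5-point grid: at least 10 | 5-point grid: above 10 | 5-point grid: exactly 10 | 1-point grid: exactly 10 |
|---|---|---|---|---|
| 5 | 36% | 14% | 22% | 4% |
| 10 | 64% | 36% | 28% | 6% |
| 15 | 86% | 64% | 22% | 4% |
| 20 | 96% | 86% | 10% | 2% |

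The rows for 15 follow by symmetry about 10 from those for 5, and the rows for 20 from those for a mean change of 0. In an arm of 20, 28% is 0.28 × 20 = 5.6 patients, 10% is 2 and 6% is 1.2.

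**The case against.** **The sentence may not mean what it literally says.** Its syntax is loose, and it can be read as a final score 10 points higher than baseline. On that reading the rule agrees with the conversion. This stands as a real possibility, but it shows that the wording leaves a change of exactly 10 undecided, and the same edit resolves it.

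**A stricter cut-off is not an error in itself.** It may come from the cited trial, which is not at hand. However, the article presents the rule as the outcome of the 2-to-10 conversion and states no wish to be stricter.

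**Stronger readings that a reader might infer, and that the article does not support:**

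- *The real threshold is 15.* This needs a 5-point scoring step, which is only implied. With finer scoring it is 11.
- *Patients who reach the meaningful change are non-responders.* This is true only of those at exactly 10. Any larger change still qualifies.
- *The rule misclassifies 28% of patients.* This takes 10 as the mean change within an arm. The sample size reproduces with 10 as the difference between arms, and both arms receive CIMT, so the mean in either arm is unknown.
- *The efficacy result is at risk.* The primary comparison uses mean change scores, and neither it nor the sample size uses the cut-off.

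**The terms differ.** Outcomes defines *clinical improvement*, while Data analyses uses *clinical response*. Equating them is plausible but not stated, so the effect on the blinding regression is conditional on it.

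**Conclusion.** The point holds in a limited form. The article's own derivation gives a meaningful change of exactly 10 on the 0–100 scale, and its rule, read literally, excludes that change.

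The range shown in the working, from 2% to 28% of patients at the boundary, rests on SD 7, a normal change, assumed mean changes of 5 to 20 and a scoring step of 1 or 5 points. None of these except the SD is fixed by the article. The upper part of the range needs the 5-point step.

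The consequence is confined to the responder label: one factor in the blinding regression, if *clinical response* there means this label, and the post-trial offers. This is a small correction to a stated threshold, and it gives no ground to doubt the main analysis.

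**What to change.** Before unblinding:

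1. In Outcomes, define clinical response for the analysis as an increase in BI from T0 to T2 of at least 10 points on the 0–100 scale. This is what the section's own conversion supports.
2. Use the same term in Outcomes and in the blinding part of Data analyses, so that the regression factor is tied to this definition.
3. Have the sponsor reconcile the post-trial offer wording in Overview with Outcomes. Which criterion should govern those offers is a clinical decision, and none is proposed here.

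The cost is a change of wording in two sections and one reconciliation. It needs no new data, no change to the sample size and no change to the primary analysis.

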### Randomization and blinding

The method of randomization will be a 1:1 permuted block randomization generated by a web-based randomization tool (www.random.org). This sequence will be done independently and remotely by a blinded investigator who will not have contact with other research procedures. The randomization will be concealed until group allocation.

After the randomization process, a blind researcher not involved with the recruitment, data collection, or intervention will perform the allocation of participants between the groups. This will be employed by concealed allocation of sequentially numbered, opaque, sealed envelopes, so that the person responsible for allocation will not have contact with patients or with the work of others. This envelope will be delivered one day before the treatment sessions to the researcher responsible for neurostimulation, who will not be involved with the other procedures for collection or data analysis.

Participants will not be identified by their real names and will not be aware of which arm of the study they are allocated to. When included in the study, they will receive a sealed, opaque envelope containing their respective identification code. In this way, the assessors will also be blind, as they will be identifying the patients by codes and will not have contact with other research procedures. The same will happen to the staff responsible for the execution of CIMT procedures. Data analysis will be conducted by a researcher not involved in any stage of recruitment, screening, assessment, or intervention.

While evaluating the efficiency of the masking mechanism [17], which is routine in studies for the treatment of stroke and other diseases related to neuromodulation, biases may occur due to inadequate blinding of several people involved in the clinical trial, or by error allocation, the effect of the treatment, or co-interventions [76]. Unlike blindness, these bias-generating consequences can be measured [77]. To this end, the example of another study using external judges [78] will be applied in this work, a final evaluation involving neurologist doctors accompanying the patients in their clinical treatment. These professionals will not be aware of behavior and interventions applied in this experiment. The imaging tests carried out for the diagnosis of vascular injury will be repeated and evaluated by these doctors at the end of intervention (T1) as a routine consultation procedure. After analysis of these imaging tests, the doctors will be asked whether they believe that the patient has suffered some consequential event which can act as an external assessment tool for a clinical trial. Reports of biased results can be examined as to whether the degree of agreement between the opinion of an external judge (neurologist) and the trialists (involved in outcome assessments and physical therapy interventions with CIMT) will be the same for both experimental and control participants.

## Intervention

### Constraint-induced movement therapy (CIMT)

The CIMT will be held immediately after the patient has received a neurostimulation session. Daily 3-hour protocol motor skills training supervised by a therapist will be applied for two weeks (10 calendar days, excluding weekends), with non-affected limb restriction for 90 % of the patient’s waking time, as advocated in previous studies with patients after stroke [79]. The motor training conducted by a physiotherapist will cover the use of the paretic limb during ADLs, with the non-paretic arm restricted by a sling. The patient will be encouraged to use the affected limb during the daily routine of his/her activities.

Patients will be encouraged to keep a journal to document their workouts, recording the training time duration, activities done with the restriction sleeve, and main difficulties. The physiotherapist responsible for the treatment will review the diary weekly, which will allow for controlling and verifying compliance in the implementation of CIMT performed by the patient. If there is a discrepancy with the principles of the technique, adjustments and guidelines will be offered for the proper conduct of the protocol. It is important to clarify that the purpose of the restriction sleeve is not to encourage a permanent change in the way the patient performs daily activities, but to encourage the concentrated and repetitive use of the paretic upper limb, seeking a “use-dependent” cortical reorganization [80].

Thus, all participants, regardless of receiving active or simulated current, will be treated with CIMT during the 10 days of neurostimulation, respecting the ethical principles to ensure therapeutic assistance to those involved.

### tDCS

The planning of the stimulation variables involves intensity, frequency of sessions, size/position of the electrodes, and duration of treatment [9]. The review of the therapeutic use of tDCS which defined safety variables was based on 21 studies (n = 278), and the conditions included depression, Parkinson’s disease, cerebral ischemia, eating disorders, alcohol dependency, and chronic pain syndromes. The application of an anodic current with identical variables to this study (involving the use of 35 cm^2^ electrodes and applying a current of 2 mA for 20 minutes for 10 days) was not related to long-term adverse or high magnitude effects [81].

The electrodes are positioned on the participant’s head at the primary motor cortex area, C3 or C4 position according to the electroencephalogram 10–20 system [82]. The anode is placed on the affected hemisphere and the cathode (reference electrode) on the supraorbital region in the uninjured hemisphere [83].

The protocol will be for 20 minutes of stimulation for 10 days (excluding weekends). The TCT neurostimulator (Research Version) developed by Trans Cranial Research Limited (Hong Kong, China) will be used, with the kit containing the neurostimulator, sponges, rubber fasteners, electrodes, and connecting cables. Electrodes are encased with 5 × 7 cm sponges and moistened with saline (0.9 % NaCl). The applied current is 2 mA, with a relative current density of 0.05 A/m2.

The protocol is identical for placebo stimulation, but the current will stop after 30 seconds from the start of stimulation, a blinding method considered reliable for several previous studies [9, 84], in which the active current is simulated (slight tingling and itching sensation) for a short period, and the effects disappear shortly after the start of the stimulation.

Although the required number and maximum sessions have not been established, we prefer to follow the model used in previous studies, which for most cases had consecutive sessions of tDCS applied for 10 days, and was able to improve motor function in different phases of stroke [24, 85, 86].

